### Enrollment and masking

A random sequence of numbers was generated by the computer under each stratify factors. Patient enrollment and investigation were personally done by 12 investigators trained by our research team. All the respondents were irreplaceable samples, meaning that they would be traced through the whole intervention period and accept investigations both in the baseline and end-line study. During intervention, the missing respondents would not be replaced by matching substitution samples, and newly screened out patients during intervention period would not be considered. Due to the trial design of provider intervention, the masking was not feasible, but the patients were not informed with the grouping information and they were not aware of what change would be given to care supply. When trial finished, we will send the database to the third player to do the analysis without giving them the group intervention information.

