### Outcomes measures

Basically, we take the period BP/GLU control rate and drug compliance (DC) as the primary outcomes. Period BP/GLU control rate is a new index we create to reflect the consistent BP/GLU control in a certain period, to replace the old index which merely consider if the BP/GLU is safe by the once time assessment. Period BP/GLU control rate takes the fluctuation degree and frequency into account; it changes reversely with the frequency and degree of BP ≥ 140/90 mm Hg (130/80 mm Hg with complications)/GLU ≥ 7.8 m mol/L (after meal) within the total times of BP/GLU assessment. The *BP control rate* is defined as the ratio of systolic pressure under 140 mm Hg (130 mm Hg with complications) among the sample (N), and CT means control times.
[figure not shown]

For the population, we use the arithmetic mean of total individual period BP/GLU control rates to evaluate the group control rate.

*DC rate* is defines as the ratio of good DC among the sample which is measured by the Morisky questionnaire. The BPs are collected at least every three months during the intervention, and the DCs are collected twice at the baseline and end-line investigation.

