### Analysis strategy

#### Statistical analysis

There are two-stage analyses in this trial. First, we will use difference-in-differences (DID) model [34] to examine the effects of the intervention; second we will use structural equation modelling (SEM) [35] to explore the hidden effecting pathway of how the intervention works.

The DID model is often used to exclude out the time effect and group differences. In the pilot study, we had mimicked the regression tendency of BP falling to ensure a similar time effect in groups. In the main study, we mainly include three explanatory variables in the regression model: group, time and interaction term between group and time. And to exclude the intra-cluster correlation (ICC) from non-independent clustering and cross-level interaction, we choose three-level regression model to control for the potential confounders of the context effect. For other repeatedly measured outcomes like BP control, lifestyle changes and professional behaviours we mainly use three-level and repeated measure multivariate analysis of variance to examine the group differences. The three levels we consider are: level 1 – individual, level 2 – cluster/village, level 3 – group. Data analysis will be carried out on the Stata (IC: 13.1). In SEM we hope to establish an explainable relationship between intervention effect of health outcome and design effect of payment system reform.

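### The level list for the difference-in-differences model has no measurement occasion beneath the patient, so the baseline/end-line pairing is lost; it also omits the town, so the net error is not fixed

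*Protocol article*

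**What the plan says.** Four parts of the protocol article bear on this.

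- **Model terms** (Statistical analysis): "we mainly include three explanatory variables in the regression model: group, time and interaction term between group and time".
- **Levels** (same section): "The three levels we consider are: level 1 – individual, level 2 – cluster/village, level 3 – group". The reason given is clustering: "to exclude the intra-cluster correlation (ICC) from non-independent clustering and cross-level interaction, we choose three-level regression model". Correlation between a patient's own measurements is not mentioned for this model.
- **Cohort** (Enrollment and masking): of the respondents, "they would be traced through the whole intervention period and accept investigations both in the baseline and end-line study"; and "the missing respondents would not be replaced by matching substitution samples". This is a closed cohort.
- **Waves** (Outcomes measures): drug compliance is one of the primary outcomes, and "the DCs are collected twice at the baseline and end-line investigation". Blood pressure follows another schedule: "The BPs are collected at least every three months during the intervention".

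For other repeatedly measured outcomes, with blood pressure control, lifestyle change and professional behaviour as examples, the Statistical analysis section says: "we mainly use three-level and repeated measure multivariate analysis of variance to examine the group differences".

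Under Sampling and randomisation, the units assigned to the three groups are six towns. The town is not among the listed levels.

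**The concern.** A regression with time as a covariate has one row per patient per wave, so a patient seen twice contributes two rows. For the model to know that those rows belong together, it needs an occasion level below the patient, or an equivalent patient effect across waves. The list starts at the individual, which makes the individual the residual level. Read as written, the two residuals of one patient are independent.

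The group-by-time term is a within-patient contrast, so the pairing is what makes a cohort more efficient than two separate surveys. Village or group intercepts do not restore it: they are constant over time and cancel from the before-after difference. At stake is the precision of both planned comparisons, treatment against control and one treatment group against the other, for outcomes measured at the two survey waves.

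**Working it through.** **The plan's own figure.** The protocol states no standard error for the difference-in-differences effect. Its only visible power statement is in the Table 2 summary: over 80% power for a 0.20 difference with 120/96 or 120/120 cases. A two-sided 5% two-proportion calculation over the stated proportions (0.5 v 0.3, 0.6 v 0.4, 0.7 v 0.5) gives 83.7–85.3% and 87.7–89.0%. The statement reproduces, but it has no bearing on this model.

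**Inputs.**
- Patients: 1641 + 332 = 1973 (The exclusion criteria). Assuming an equal split and no overlap, n = 1973/3 ≈ 658 per group.
- Towns: six in three groups, so two per group.
- Outcome scaled to SD 1.
- ρ, the correlation of a patient's baseline and end-line values: not in the document; 0.3, 0.5 and 0.7 assumed.
- t, the town-by-period variance as a share of the total: not in the document; varied.

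**Step 1: pairing alone.** The contrast is a difference of two mean changes.
- Waves independent: variance = 4/n, SE = √(4/658) = 0.078.
- Waves paired: variance = 4(1−ρ)/n.
- Ratio of SEs = 1/√(1−ρ).

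**Step 2: add the town.** With two towns per group and two waves, town-by-period variation adds 2t to the true variance: 4(1−ρ)/n + 2t. The listed model still reports 4/n. The two are equal when t = 2ρ/n.

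| ρ | SE, independent | SE, paired | Ratio (t = 0) | Break-even t | Ratio at t = 0.005 |
|---|---|---|---|---|---|
| 0.3 | 0.078 | 0.065 | 1.20 | 0.0009 | 0.65 |
| 0.5 | 0.078 | 0.055 | 1.41 | 0.0015 | 0.68 |
| 0.7 | 0.078 | 0.043 | 1.83 | 0.0021 | 0.72 |

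Example at ρ = 0.5, t = 0.005: true SE = √(4×0.5/658 + 0.01) = 0.114, and 0.078/0.114 = 0.68.

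**Step 3: simulation.** 3000 runs per setting with no true effect: 2 groups × 2 towns × 10 villages × 33 patients × 2 waves, village ICC 0.03 (assumed), continuous outcome. Results are for ρ = 0.3 / 0.5 / 0.7.
- t = 0: listed SE over true SD is 1.24 / 1.43 / 1.87; false positives are 1.7% / 0.4% / 0.0% against a nominal 5%.
- t = 0.005: the ratio is 0.65 / 0.67 / 0.72; false positives are 20% / 18% / 16%.
- t = 0.005 with pairing used but the town still left out: false positives are 30% / 35% / 46%.

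**The case against.** **Repeated-measures analysis may already cover these outcomes.** The Methods part of the Abstract gives repeated multivariate variance analysis for outcome differences without restriction. The list in Statistical analysis is open-ended, and the process measures place compliance with medication beside lifestyle change. This stands in part. Blood pressure control and lifestyle change are outside the point, and for drug compliance the text is ambiguous. But the list is introduced as outcomes other than those in the regression, and drug compliance and SF-36 are not named in it.

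**The individual may stand for a change score.** That would preserve the pairing, but a change-score model has no time term and this one does.

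**A condensed article leaves random effects to an analysis plan.** True of detail that is merely absent. Here the levels are enumerated, and the enumeration does not fit the design.

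**The loss may not matter.** For an effect as large as the 20 points used in the sample-size section (there for continuity of clinical service), the largest possible binary variance gives SE = √(4×0.25/658) = 0.039 and 0.20/0.039 = 5.1. Power is then close to 100% without pairing, if there is no town-by-period variation. This stands for large effects only.

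**A reader might infer that the intervals will be too wide and the test conservative.** The documents do not support that. The same list omits the town, which pulls the other way, and a very small town-by-period variance reverses the result.

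**Conclusion.** The point holds in a limited form. For outcomes measured at two waves and analysed by the stated regression, the listed levels have no place for occasions within patients. On its own, this overstates the group-by-time standard error by a factor of 1.20 to 1.83 for ρ from 0.3 to 0.7. That range is an assumption, as is the equal split of 1973 patients behind the absolute figures.

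The net direction of error is not established. A town-by-period variance of 0.0009 to 0.0021 of the total cancels the overstatement, and at 0.005 the reported error is about a third too small. Two errors that may offset by chance do not make a valid model.

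Three stronger readings should be avoided:
- That the model lacks a patient level. The individual is level 1; what is missing is the occasion beneath it.
- That the protocol declares the waves independent. This follows from the listed levels; it is not stated.
- That a given amount of power is lost for drug compliance. The protocol gives neither a baseline compliance rate nor a target difference for it. The rate below 15% in the Trial setting section is for good control and good compliance together.

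This should be corrected before the end-line analysis.

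**What to change.** Make one edit to the Statistical analysis section with two parts.

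1. For drug compliance, SF-36 and any other outcome taken at baseline and end-line, define level 1 as the measurement occasion and level 2 as the patient, with village above. Equivalent options are to analyse each patient's change, or the end-line value adjusted for the patient's own baseline value.
2. Replace group as the top level with the allocated town, including town-by-period variation, and keep group as a fixed effect.

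The first part must not be made without the second: in the simulation at t = 0.005, using the pairing without the town raised false positives to 30–46%. The same edit should say whether drug compliance belongs to this regression or to the repeated-measures analysis.

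**Cost.** No new data or patients are needed, only some sentences and extra random-effect terms. The binary mixed model is slower to fit and its effect is conditional on the patient, so a marginal risk difference should be reported beside it. With six towns, two per group, the town-by-period variance will be poorly estimated. Honest intervals may be wide, and the report should say so.

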## Methodology

### Study design

A clustered randomised controlled trial was used. Nearly 60 clusters/villages in 6 towns and 200 professionals from three levels were intervened, and around 6000 chronic patients were enrolled in this trial. We re-designed the health policy by giving initials to change their delivery and payment system on chronic diseases. There were two basic intervention modes: (1) care integration (MDT and MIP), which was to integrate different caregivers aiming to reshape the solitaire county–town–village service frame into an integrated health care delivery system; (2) payment integration (SGB–P4P), which was to integrate between the delivery system and medical insurance payment system by alternating the original fee-for-service system into a pre-paid system. This strategy aimed to create incentives to help the suppliers to act more willingly or actively. In accordance, the 60 clusters were categorised into three groups: two treatment groups which implemented each of the above strategy; and one control group with no interventions to serve as a natural blank comparison.

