### Hypothesis

The whole hypothesis was made based on the evolving model of Andersen's service utilisation behaviour model and Donabedian's structure-process-outcome paradigm to assess the health quality [27, 28]. We modified the health system structure referring to some suggested modification to adapt to the chronic cases [29–31]. We made two basic assumptions under the transduction pathways from hypothesis to conclusion: (1) the integrated health service delivery would improve health outcomes through providing more coordinated care, and the system efficiency would then improve from better primary and community care; (2) the payment system would help to change the supplier behaviours and exemplify the outcomes. Assumption 1 would be proved from comparing treatment groups with the control group; and Assumption 2 would be proved from comparison within this two treatment groups (see Figure 2).

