#### Multidisciplinary team service

The MDT was developed to help both the primary and hospital care and suppliers integrate under the situation of scarce human resources. Considering the unique county–township–village human resource distribution structure in rural area, we designed a “double L” team – a unique structure to connect three service levels from both horizontal and vertical direction. The upper vertical ladder connected the clinical physicians between county–township level, and the lower vertical ladder connected the primary caregivers between township–village level; and the interphase was the connection of clinical and primary staff through coordination management in township level. In this trial, we enrolled in 15 doctors in each county hospital, 2 from out-patient and 3 from in-patient Departments of Endocrinology, Neurology and Cardiology, to take care of the continuous treatment and contact with the community doctors. In every intervened town we enrolled six staffs: two physicians, one responsible for out-patient and one for in-patient; three primary caregivers, mainly took care of screening, following up and monitoring the chronic patients; and also one team manager/coordinator, to help the team communication and information delivery. In every cluster of the intervened town we enrolled all the village clinicians to help the neighbourhood follow-up. By this means we formed a MDT from different disciplines as primary care, clinical service and management, and also from different organisations as county hospital, township hospital and village clinics; and also made sure there to be at least 17 clinicians, 10 primary caregivers and 4 management staff in every community to serve the chronic patients (see Figure 3).

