### Sampling and randomisation

Six towns were selected randomly from the 24 rural communities and then were categorised into three groups with a combined consideration of population size, social development and distance. Because there were obvious potential confounders in social experiment, the towns were first categorised into two types based on comprehensive consideration of socio-economic development level and hospital ability, two basic confounders which we assumed high relevance with the intervention outcome. The socio-economic development level mainly indicated the patient population, their per capita income and average distance from the location to downtown (translated into traffic time by public transportation). The hospital ability represented resource possession and staff skills. Second, every two towns of each type were randomly assigned into treatment/control groups to ensure group comparability. These two steps were done to make sure towns comparable both within groups and within cluster types in case of different comparison need.

In patient sampling, we used three-stage stratified random sampling strategy instead of propensity scoring matching, concerning the complexity of sampling and excessive workload. We chose gender, age and risk level as the three stratify factors. Risk level was a comprehensive factor that summing up the BP/GLU level as well as the possible risky factors due to the patient lifestyle. The hypertension and diabetes II patients were divided into three and two risking groups before the baseline, and we stratified the patient library mainly in accordance with the original files but with a slight alternation based on professional re-assessment after personal contact at the baseline.

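### The stated model levels are individual, village and group; town, the unit that was assigned, is missing, so false-positive rates can exceed 5% by an amount set by town-level change over time

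*Protocol article*

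**What the plan says.** **Assignment.** The Sampling and randomisation section states: "Six towns were selected randomly from the 24 rural communities and then were categorised into three groups". Towns were sorted into two types by socio-economic level and hospital ability, and then "every two towns of each type were randomly assigned into treatment/control groups to ensure group comparability". No section describes randomising villages.

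**Delivery.** The Multidisciplinary team service section organises the intervention by town: "In every intervened town we enrolled six staffs", together with all village clinicians of that town.

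**Analysis.** The Statistical analysis section gives the DID terms: "we mainly include three explanatory variables in the regression model: group, time and interaction term between group and time". It chooses a three-level regression in order to deal with intra-cluster correlation, and names the levels: "The three levels we consider are: level 1 – individual, level 2 – cluster/village, level 3 – group". Town appears neither as a level nor as an explanatory variable.

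**Scale and use.** The Study design section gives "Nearly 60 clusters/villages in 6 towns and 200 professionals from three levels were intervened". The Hypothesis section says "Assumption 1 would be proved from comparing treatment groups with the control group", and uses the same word for Assumption 2, which compares the two treatment groups with each other.

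**The concern.** The three-level model is there to handle clustering, but the levels listed omit the one at which assignment was made. Group cannot stand in for town: it has three units and is the treatment contrast itself.

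Villages in one town share a township hospital, a team and, where it applies, a payment arrangement. If outcomes in one town improve or worsen over the study for local reasons, about 10 villages move together. A village-level test reads that shared movement as about 10 separate confirmations.

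At stake are both main conclusions. Assumption 1 rests on four treated towns against two control towns, and Assumption 2 on two towns against two.

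**Working it through.** **1. The plan's own figure.** The note to Table 2 says 120/96 or 120/120 cases give over 80% power for a difference of 0.20. For two independent proportions at two-sided 5% (sidedness is not stated, so assumed):

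| Proportions | 120/96 | 120/120 |
|---|---|---|
| 0.5 v 0.3 | 0.851 | 0.890 |
| 0.6 v 0.4 | 0.837 | 0.877 |
| 0.7 v 0.5 | 0.853 | 0.890 |

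The figure reproduces when patients are treated as independent, that is, with no allowance for village or town.

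**2. Inputs for the error rate.**
- From the article: 6 towns; about 60 villages, so 60/6 = 10 per town; 1641 + 332 = 1973 patients, so 1973/60 ≈ 33 per village.
- Read from loose wording: two towns per group.
- Assumed, because the article gives no ICC: town share τ of the variance in *change* from 0 to 0.05, and village share ν = 0.02. Shares of variance in change are the relevant ones, because the DID effect is the group × time term.

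**3. Formula.** With J = 10 villages, m = 33 patients and e = 1 − τ − ν, the variance of a town's mean change is

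true: τ + ν/J + e/(Jm)

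as seen by a village-level analysis: (τ + ν)/J + e/(Jm)

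At τ = 0.01: true 0.01 + 0.002 + 0.97/330 = 0.01494; as analysed 0.003 + 0.97/330 = 0.00594. The standard error is too small by a factor √(0.01494/0.00594) = 1.59. The normal approximation gives a type I error of 2[1 − Φ(1.96/1.59)] ≈ 0.22.

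**4. Simulation.** No true effect, 40,000 runs per row, ν = 0.02. The village-level test uses 57 df and the town-level test 3 df. Results for Assumptions 1 and 2 are nearly identical.

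| Town share of variance in change | Village-level test | Town-level test |
|---|---|---|
| 0 | 5% | 5% |
| 0.001 | 7% | 5% |
| 0.005 | 15% | 5% |
| 0.01 | 23% | 5% |
| 0.02 | 33% | 5% |
| 0.05 | 47% | 5% |

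With ν = 0 the village-level figures from 0.005 upward are 21%, 30%, 41% and 53%.

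**5. Allowing for balance by town type.** Suppose each group has one town of each type and type explains half of the town variance in change (an assumption). The village-level figures at 0.005, 0.01, 0.02 and 0.05 then fall to about 10%, 13–14%, 19–22% and 29–33%. The ranges reflect whether the type effect is a fixed offset or drawn at random.

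**6. What the assignment alone can support.** These counts need no ICC.
- No stratification, Assumption 1: C(6,2) = 15 choices of control towns, smallest p = 1/15 = 0.067.
- No stratification, Assumption 2: C(4,2) = 6, smallest two-sided p = 2/6 = 0.33.
- One town of each type per group, Assumption 1: 3 × 3 = 9, smallest p = 1/9 = 0.11.
- One town of each type per group, Assumption 2: 2 × 2 = 4, smallest two-sided p = 2/4 = 0.50.

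**The case against.** **DID already removes town differences.** It removes the stable ones. A reader might infer that terrain, wealth or hospital size as such would be mistaken for an effect; the planned model does not support that, because these cancel in the change. Town-specific change remains, and it is the variance used above.

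**The size is unknown.** This stands. The article gives no ICC, and at a town share of zero the missing level causes no inflation. Sorting towns by type may also absorb part of the variance, as step 5 shows. The plan gives no ground for assuming that either removes the problem entirely.

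**Listing group as a level spoils the effect estimate.** A reader might infer this because group is also fixed. It does not follow: a random intercept for group would compete with the group main effect, whereas the effect tested is group × time. Listing group is poor specification, but the damage comes from omitting town.

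**Repeated readings have no level.** This too is tempting and is largely answered in the article. The same section names repeated-measures multivariate analysis of variance for repeatedly measured outcomes, and the primary BP outcome condenses readings into one period rate per patient.

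**The limitation is acknowledged.** The Discussion concedes that randomisation was compromised and that the strength of proof may be reduced. It does not mention the unit of analysis or false positives.

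**Conclusion.** The structural point holds on the text: towns were assigned, the intervention is delivered by town, and the stated model has village and group but no town. This is a rule the article states, not detail left to another document.

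The size is conditional. Type I error is about 15% to 47% for a town share of variance in change of 0.005 to 0.05, given a village share of 0.02, two towns per group and no gain from balancing by type. It is lower with such a gain, and at a zero town share towns add nothing. So the p-values may be much too small; the article does not allow one to say that they will be.

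Nor do the limits in step 6 show that no test can reach 0.05. They belong to a re-randomisation test, which the plan does not propose; a town-level t-test can fall below 0.05 under its distributional assumptions. The limits do show how little two towns per group can establish by assignment alone.

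**What to change.** - Replace the third level, group, with town, and keep group as a fixed effect only.
- Base the primary inference for both assumptions on the six town-level mean changes, with the pooled between-town variance and 3 df (critical t 3.18, against 2.00 at 57 df). If town type is adjusted for, use 2 df (critical t 4.30). A town intercept alone would not be enough, because the group × time effect must be judged against variation between towns in change.
- Report estimates with those intervals, and label village-level p-values as descriptive.
- In the Hypothesis section, replace the claim that the assumptions would be proved with a statement of the limited inference that two towns per group allow, citing the re-randomisation limits.

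The change needs wording and code, and no new data. The price is precision. For Assumption 2 the 3-df intervals average about 1.5 times the width of the village-level ones at zero town variance, 2.4 to 2.8 times at a share of 0.01, and 4.0 to 4.6 times at 0.05. The conclusions will be more cautious.

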## Trial setting

### Geography remoteness and economy weakness

Qianjiang District is a typical rural area locates in southeast Chongqing, the only municipality who sits in the deeper part of southwest China and thus is less developed compared to the other three municipalities. Qianjiang had a population size of 550,000 people whose average income per capita per year in the past five years was under US$480, relatively half of the whole nation's spectrum (data resource: Qianjiang District National Economic and Social Development Statistics Bulletin 2001–2012). Qianjiang has in total 30 communities and 24 of them are rural ones. The average town population size is about 12,000, and every town has around 10 villages. Rural people accounted for 80% of the total population. Over 90% of the rural people have enrolled in the New Rural Cooperative Medical Scheme, which allow them to get nearly 60% (2012) reimbursement of the total in-patient medical expenditure from the medical insurance fund. The unique mountainous terrain causes the average travel time from rural towns to downtown unexpectedly high, varying from 0.5 hour to 6 hours (by mass transportation), walking and transferring time not included (see Figure 1).

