### Human resource shortage

Two major county hospitals and 24 township hospitals took the responsibility of medical treatment for rural chronic patients in this area. There were about 20 doctors/licensed practicing physicians from Departments of Endocrinology, Neurology and Cardiology in each county hospitals, which mainly deal with hypertension, diabetes and the complications such as stroke, coronary heart disease, diabetic foot and diabetic eye diseases. In each township hospital, there were about five medical staff and three primary care staff who provide basic medical treatments and regular follow-ups; in each village, there were one or two doctors who provide simple medical treatments and prescribe basic medicines like Captopril or Nifedipine. In all, the 40 doctors from county hospitals and 8 medical staff from each township hospital took care of over 90% of the primary/secondary/tertiary care for all the chronic patients of its own town. It is not difficult to conclude that, the inadequate health human resource, both in quality and quantity, is one of the major problems that hinder the improvement of quality care.

To sum up, Qianjiang rural area has problems of extremely low availability of access and human resource, thus create terrible consequences as: (1) decreasing quality of care; (2) dropping down of QOL; and (3) raising up of the disease burden. To make the inequity problem even worse, due to inconvenient medical consultancy and reluctance visits, poorer people often get severe complications before they are willing to see a doctor, and less poor people are often out of appropriate control to seek for higher medical treatment. This situation would create the most harmful result of the patient flow disorder and leap of medical expenditures, and also would diminish the original health resource distribution and system efficiency, which we believe is the worst tendency in nowadays rural areas no matter where they come from.

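### The single set of model levels (individual, village, group) does not fit supplier outcomes measured on staff: county and township staff have no village, and town is not a level

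*Protocol article*

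**What the plan says.** Statistical analysis assigns a method to a mixed list of outcomes: "For other repeatedly measured outcomes like BP control, lifestyle changes and professional behaviours we mainly use three-level and repeated measure multivariate analysis of variance". It then defines the levels for that method, with no separate version for staff: "The three levels we consider are: level 1 – individual, level 2 – cluster/village, level 3 – group".

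The staff are described elsewhere in the Protocol article:

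- **County.** Multidisciplinary team service enrols 15 doctors in each county hospital. Human resource shortage names two such hospitals.
- **Township.** "In every intervened town we enrolled six staffs".
- **Village.** All village clinicians in intervened towns are enrolled, and "in each village, there were one or two doctors who provide simple medical treatments".

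Sampling and randomisation assigns towns, not villages, to the groups. Study design gives the totals: "Nearly 60 clusters/villages in 6 towns and 200 professionals from three levels were intervened". The same section describes "one control group with no interventions to serve as a natural blank comparison".

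**The concern.** A level in a multilevel model has to be something every analysed person belongs to. A patient has a village. A township physician works for a town's hospital, and a county doctor for a county hospital. The article gives no rule that places either in a village, and it does not say how county doctors map to groups, so their third level is undefined as well.

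Supplier cooperative behaviour is one of the outcomes listed in the Abstract, and the second assumption under Hypothesis is that payment changes supplier behaviour. The team design exists to connect county, township and village staff. An analyst who follows the stated levels must leave out the county and township staff or give them villages arbitrarily.

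The omission of town matters too. Staff in one town share a township hospital and a team. If their answers are alike for that reason, a model without town treats villages in the same town as independent, and the standard error of the group comparison is too small. The documents give no figure from which to size this.

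**Working it through.** **Inputs**

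- County doctors: 2 hospitals × 15 enrolled = 30. Human resource shortage gives full staffing as 40.
- Township staff: 6 enrolled per intervened town. Full staffing is 8 per township hospital.
- Village doctors: 1–2 per village. Geography remoteness and economy weakness says "every town has around 10 villages", hence 10–20 per town.
- Towns: six in all. Four are treated if each of the three groups has two (inferred; Table 4 is not shown).

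**Step 1. The stated 200**

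Count = county + (township staff × towns) + (10 to 20 × towns).

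| Basis | Towns | Sum | Total |
|---|---|---|---|
| Full staffing | 6 | 40 + 48 + (60 to 120) | 148–208 |
| Enrolled county, full township | 6 | 30 + 48 + (60 to 120) | 138–198 |
| Itemised enrolment | 6 | 30 + 36 + (60 to 120) | 126–186 |
| Full staffing | 4 | 40 + 32 + (40 to 80) | 112–152 |
| Itemised enrolment | 4 | 30 + 24 + (40 to 80) | 94–134 |

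The first row reproduces 200 at (200 − 88)/60 = 1.87 doctors per village, and the second comes within 2 of it. Both count all six towns, control towns included. Neither four-town row reaches 200.

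**Step 2. Enrolled staff without a village**

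- Four towns: 30 + 24 = 54. 54/134 = 40% and 54/94 = 57%.
- Six towns: 30 + 36 = 66. 66/186 = 35% and 66/126 = 52%.

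The overall range is 35–57%.

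**Step 3. Village doctors: can village variance be estimated?**

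Take two occasions per doctor and assumed variances of 0.10 (village), 0.40 (doctor) and 0.50 (residual). None of these comes from the documents. For each village V = 0.10·J + 0.40·D + 0.50·I, where J links all observations in the village, D links those of one doctor and I is the identity. The information for variances a and b is ½·tr(V⁻¹MₐV⁻¹M_b), where M is the matrix J, D or I that belongs to each variance, summed over villages.

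| Villages with two doctors | SE of village variance, 40 villages | SE, 60 villages |
|---|---|---|
| None | not separable (rank 2 of 3) | not separable (rank 2 of 3) |
| 25% | 0.23 | 0.19 |
| 50% | 0.17 | 0.14 |
| All | 0.12 | 0.10 |

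Once some villages have two doctors the model is identified, but the standard error is about as large as the variance of 0.10 or larger.

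**Step 4. Which supplier measures are affected**

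Under Process measures, communication frequency and staff satisfaction are naturally measured on staff, and Project costing lists a staff questionnaire among the data sources. Unnecessary exams per capita, referrals, and referral and waiting times can be counted per patient and nested in villages through the patients.

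**The case against.** A reader might infer that the stated model cannot be fitted at all. The documents do not support that. Villages have one or two doctors, and with a mix the variances are identified, though weakly. If every village had one doctor, only the split between village and doctor variance would be lost: their sum is still estimated, and the group-by-time contrast does not need the split. Several supplier measures also fit the patient model. All of this stands. What remains is that county and township staff have no second-level unit.

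A reader might also infer that 200 professionals cannot be reached. That fails too, because full staffing over six towns gives 148–208. Multidisciplinary team service further speaks of four management staff per community, while its six township staff include one manager. If the other three are separate people in each town, the six-town enrolment count becomes 126 + 18 = 144 to 186 + 18 = 204. The same addition in four towns gives 106–146, still short of 200. Nor can the gap be turned into a loss of precision: Sample size and power calculation rests nothing on 200 staff, and the 94–134 count leaves out control staff, who would be needed in any group comparison.

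It is fair to add that the article is condensed and says it will mainly use these methods, that cooperation is also examined by an integration questionnaire (Structure measures) and a process evaluation, and that Table 5, which defines the outcomes, is not shown. These points limit the consequence. They do not remove it, because the article does more than stay silent: it states one set of levels and names professional behaviours among the outcomes they serve.

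**Conclusion.** The point holds for supplier outcomes measured on staff. The stated levels have no place for county and township staff, about 35–57% of those enrolled under Multidisciplinary team service. They rest on village units of one or two doctors that say little or nothing about village variance, and they leave out town, the unit assigned to groups. The percentages assume about 10 villages per town and four or six towns. The standard errors in Step 3 depend on assumed variances and show only the order of size.

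Secondarily, Study design describes about 60 villages and 200 professionals as intervened on, although one of the three groups has no intervention. The 200 is compatible with all staff over six towns but not with the itemised enrolment: at most about 134 in four treated towns and 186 in six, unless additional managers are counted.

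The primary outcomes are measured on patients and are not touched.

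**What to change.** 1. For supplier outcomes measured on staff, state a separate structure: staff within institution (village clinic or township hospital) within town.
2. Report county-hospital staff separately by hospital. Make a group contrast for them only if they can be assigned to a group, and say how.
3. State which supplier measures are per staff member and which per patient, and analyse the per-patient ones with the patient model.
4. In Study design, give the numbers of villages and professionals by level and by group, separating intervened from control.

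The cost is a little more analysis work, some wording, and a smaller stated number of intervened staff. With six towns the town variance will be imprecisely estimated, which should be acknowledged when staff results are reported.
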